#### Congruency between desired and actual role in the decision process and satisfaction with the actual role

The congruence between the desired and actual role in the decision-making process and satisfaction with the actual role played is assessed by the Control Preferences Scale (CPS) [40, 41]. The CPS was designed to measure the degree of control that patients want to assume in physician–patient interactions and has often been used in studies on decision support. The items were adapted to the decision situation of *BRCA1/2* mutation carriers by replacing the term “treatment” with “prevention strategy”. The desired role will be measured at baseline and the actual role at T2 (12 weeks after inclusion). The difference between these two measurements reflects the congruence between desired and actual role. One item will be added to the CPS to measure satisfaction with the actual role played at T2.

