### Objectives {7}

The EDCP-BRCA study aims to assess the effectiveness of decision coaching combined with a decision aid. The main hypothesis is that *BRCA1/2* mutation carriers who receive nurse-led decision coaching and a decision aid will show a higher congruence between the role they preferred to play in the decision-making process and the role they actually played. Secondly, we hypothesize that women who receive nurse-led decision coaching combined with a decision aid show higher satisfaction with the role they played in the decision-making process when compared to the control group. Additional objectives of the study are to evaluate whether decisional conflict and psychological burdens can be decreased and knowledge about the different preventive options can be increased.

Additionally, process evaluation will be conducted alongside the study to identify the barriers and facilitating factors of implementation. Secondly, the nurses and participating women are asked to share their experiences of the intervention. Finally, the process evaluation aims at investigating the underlying mechanisms of the intervention in relation to the context and interpreting summative results considering the impact of the intervention.

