### Outcomes {12}

The primary outcome of the study is the congruence between the preferred and actual role in the decision-making process as measured by the Control Preferences Scale (CPS) [40, 41]. Secondary outcomes are satisfaction with the actual role, decisional conflict (Decisional Conflict Scale (DCS)) [42, 43], knowledge and attitude towards preventions strategies (Multidimensional Measure of Informed Choice (MMIC)) [44, 45], stage of decision-making (Stage of Decision Making Scale (SDMS)) [46, 47], symptoms of anxiety and depression (Hospital Anxiety and Depression Scale (HADS)) [48, 49], coping self-efficacy (Coping Self-Efficacy Scale (CSES)) [50], subjective impact of the test result (Impact of Event Scale (IES)) [51, 52], and self-concept of *BRCA1/2* carriers (BRCA Self-Concept scale (BRCA-SC)) [53]. The instruments that will be used to measure these outcomes will be obtained at three different time points. Baseline measures will be obtained before randomization within a week of inclusion in the study, t1 measures will be obtained 12 weeks after inclusion, and t2 at 6 months after inclusion in the study. Table 1 displays the outcome parameters and time points for outcome measurements.

**Table 1 Tab1:** Outcome parameters

	Study period						
	Enrolment		Allocation	Post-allocation			
Timepoint		Directly after inclusion		1 week after inclusion	Within 3 weeks after inclusion	12 weeks after inclusion	6 months after inclusion
Enrolment							
Eligibility screen	X						
Informed consent	X						
Allocation			X				
Interventions							
Decision aid				X			
Decision coaching					X		
Assessments		t0				t1	t2
Control Preferences Scale							
Desired role		X					
Actual role						X	
Satisfaction						X	
Decisional Conflict Scale		X				X	X
Multidimensional Measure of Informed Choice							
Attitudes		X				X	X
Knowledge		X				X	X
Stage of Decision Making Scale		X				X	X
Hospital Anxiety and Depression Scale		X				X	X
Coping Self-Efficacy Scale		X				X	X
Impact of Event Scale		X				X	X
BRCA Self-Concept Scale		X				X	X

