### Sample size {14}

The sample size calculation for the summative evaluation is based on an assumed small to moderate effect of the intervention (Cohen’s *d* = 0.3) in a two-sided *t*-test between two groups [28]. It accounts for a drop-out rate of 30%, a power of 0.8 and an alpha error of 0.05. Based on these numbers, the software G*Power [55, 56] yielded a total *n* = 398 (199 participants per group).

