## Statistical methods

### Statistical methods {20a}

Baseline data will be analyzed to guarantee comparability of both groups. Mean differences of the primary outcome in both groups (congruence between preferred role at baseline and actual role in the decision-making process at t1) will be compared using an independent samples one-sided *t*-test with the group allocation as the independent variable. All secondary outcomes will be analyzed via independent samples *t*-tests, Chi-square tests, or nonparametric tests in case of non-normality. Beyond group allocation, demographic data will be used as the independent variable. All data analysis will be performed with SPSS and R.

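### The primary congruence score is defined only as a difference, with no absolute value, match rule or direction of benefit, so the planned t-test taken literally compares mean role, not congruence

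*Protocol article*

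**What the plan says.** Objectives {7} states the main hypothesis: women given coaching and the decision aid "will show a higher congruence between the role they preferred to play in the decision-making process and the role they actually played". Outcomes {12} makes the same concept primary: "The primary outcome of the study is the congruence between the preferred and actual role in the decision-making process", measured with the Control Preferences Scale (CPS).

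The subsection on the CPS gives the timing, "The desired role will be measured at baseline and the actual role at T2 (12 weeks after inclusion"), and then the only scoring rule in the article: "The difference between these two measurements reflects the congruence between desired and actual role".

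Statistical methods {20a} gives the analysis. "Mean differences of the primary outcome in both groups" "will be compared using an independent samples one-sided *t*-test with the group allocation as the independent variable".

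No section takes the absolute value of the difference, says what counts as a match, gives the order of subtraction, or says which tail of the one-sided test means benefit.

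**The concern.** Congruence is best when actual and desired role coincide, and worse on either side. A plain difference is zero at the best value and moves away from it in both directions. Its mean therefore does not rise or fall steadily with congruence: one woman two steps more active than she wished and another two steps more passive average to zero, as if both were perfectly matched.

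The hypothesis of higher congruence and a one-sided test both need a score with a single good direction. If the rule is applied as written, the primary test asks whether coaching moves women towards a more active or a more passive role. That is a different question from whether they played the role they wanted. A real gain could go undetected, or a general shift in role could be read as success.

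**Working it through.** **Inputs from the protocol article.** Sample size {14}: d = 0.3, alpha 0.05, power 0.80, 30% drop-out, total 398 (199 per group). Outcomes {12} and Baseline data and allocation: baseline questionnaires are returned before randomisation.

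**Number analysed per arm.** A one-sided t-test with d = 0.3, alpha 0.05 and power 0.80 needs 139 per group, 278 in total. Then 278/0.70 = 397.1, or 398 with equal groups, which is the article's figure. So 139 completers per arm are used below. (Sample size {14} describes the calculation as "in a two-sided *t*-test between two groups". That would need 176 per group, 352 in total, and 352/0.70 = 502.9, or 503. This conflict over sidedness is a separate matter.)

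**What the plain difference estimates.** Let P be the desired role, A the actual role and D = P − A. P is measured before randomisation, so it has the same expectation in both arms, and

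E(D | intervention) − E(D | control) = −[E(A | intervention) − E(A | control)].

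Desired role drops out, and the contrast is in mean actual role alone.

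**Illustrations.** The article gives no role distributions, so those below are assumptions. D takes the values −2, −1, 0, 1, 2, with the probabilities listed in that order. A higher code is assumed to mean a more active role, so negative D means more active than wished. With n = 139 per arm, d = difference in means / pooled SD, and the expected t is d × √(139/2) = d × 8.337. Rejection rates come from 20,000 simulated trials per case.

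1. *Symmetric mismatch, congruence improves.* Control (.10, .20, .40, .20, .10), intervention (.05, .15, .60, .15, .05). Exact match rises from 40% to 60%.
   - Mean D is 0 in both arms, so d = 0 and the test rejects in 5% of trials, its nominal level.
   - Mean |D| falls from 0.80 to 0.50. The variances are 1.20 − 0.64 = 0.56 and 0.70 − 0.25 = 0.45, and the pooled SD is √0.505 = 0.711. So d = 0.30/0.711 = 0.42 and the expected t is 3.52. Power is 94% two-sided and 97% one-sided.
2. *Mismatch mostly one way, congruence improves.* Control (.02, .08, .54, .26, .10), intervention (.02, .08, .70, .15, .05). Exact match rises from 54% to 70%.
   - Mean D falls from 0.34 to 0.13; pooled SD 0.774, d = 0.27, one-sided power 73%.
   - Mean |D| falls from 0.58 to 0.37; pooled SD 0.655, d = 0.32, one-sided power 84%.
3. *All mismatch one way, congruence improves.* Control (0, 0, .54, .36, .10), intervention (0, 0, .70, .25, .05). D equals |D| for every woman, so the two tests are identical: 80% power two-sided, 88% one-sided.
4. *Shift past the wished-for role, congruence worsens.* Control (.05, .10, .60, .20, .05), intervention (.15, .25, .45, .10, .05). Exact match falls from 60% to 45%, and mean |D| rises from 0.50 to 0.75.
   - Mean D moves from +0.10 to −0.35. If more activity is the benefit direction, the one-sided test is significant in 99% of trials. With the opposite direction it is significant in essentially none.
   - The test on |D| shows the intervention as worse in 89% of trials (one-sided).

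**The case against.** The strongest reply is that the article never calls the difference signed. In ordinary usage a difference can be the size of a gap. Statistical methods {20a} names congruence as the quantity averaged. A hypothesis of higher congruence and a one-sided test make sense only for a score with one good direction, so they can be read as evidence that distance was meant. A journal article also commonly leaves instrument coding to a fuller plan.

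Much of this stands. It rules out the stronger reading that a reader might infer, namely that the protocol has fixed a signed score and the primary analysis is therefore invalid. It does not remove the point, because the article does not simply omit the scoring rule. It states one, and an analyst who follows it with the stated comparison of means could get a wrong primary result.

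The size is also open to challenge. Case 1 is symmetric by construction, so the plain difference must show nothing. The only role figures in the article (Background, breast cancer patients) are about 63% preferring patient-centred or shared decisions against 54% experiencing them. That is a net shortfall in involvement. These are marginal percentages and do not exclude mismatch both ways, but they do not support symmetry. On the other side, the Background cites a trial in which adding coaching to a decision aid led to a more active experienced role, so a general shift in role is a plausible effect here.

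Finally, a reader might infer from case 4 that the plan would reward a loss of congruence. The document does not support that as stated: it names no direction of benefit, and the false success appears only if more activity is taken as benefit.

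**Conclusion.** The point holds in a conditional form. The rule as written leaves open whether the difference is plain or absolute and which direction is better. Under the plain reading, the primary test contrasts mean actual role and does not test the hypothesis in Objectives {7}.

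The loss depends on assumed distributions. With 139 per arm it ranges from none (all mismatch one way), through 73% against 84% one-sided power (mostly one way), to about 5% against 94% two-sided (symmetric). Under the absolute reading there is no distortion, only a missing statement. The ambiguity still needs resolving, because it concerns the primary outcome and the two readings can point in opposite directions on the same data.

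**What to change.** In the CPS subsection and in Statistical methods {20a}, define the primary score as |actual role at 12 weeks − desired role at baseline| on the ordered CPS categories, with 0 meaning congruent. State that lower is better and that the t-test is on this score. Report the signed difference descriptively only, to show the direction of mismatch. If the absolute difference was intended all along, one explicit sentence is enough.

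The proportion with an exact match and an analysis adjusted for desired role are optional supporting analyses.

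No new data or extra visits are needed. Recruitment has begun (Trial status), so the change should follow the route in Protocol amendments {25}: funder, study centres and registry entry. It should be fixed before the outcome data are analysed, so that the choice of score cannot depend on the results.

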#### Decisional conflict

Decisional conflict will be assessed using the Decisional Conflict Scale (DCS) [42, 43]. It captures uncertainty in health-related decisions. The DCS comprises 16 items and includes five subscales: information, personal uncertainty, clarification of values, support or pressure from others, and perception of the quality of the decision process. The items are scored on a five-point Likert scale (1 = strongly agree to 5 = strongly disagree). The German translation of the DCS showed good psychometric properties [43]. The DCS will be used at T1, T2, and T3.

#### Attitude and knowledge

Attitudes towards prevention strategies will be measured by the attitudes subscale of the Multidimensional Measure of Informed Choice (MMIC) [44, 45]. The MMIC requires generating items to measure knowledge in the field of interest, while the attitude items are generic and usable for all types of scenarios. Knowledge about the different prevention strategies available to *BRCA1/2* mutation carriers will be tested using a set of 15 items developed by experts in the field developed in a prior study. For each item, the participant has to indicate whether a statement is correct or false. The knowledge test includes questions about lifetime cancer risk for mutation carriers, benefits and harms about each preventive option, as well as lifestyle-related questions. A choice is rated as informed as soon as women have adequate knowledge (at least eight correct knowledge items) about the option and a positive attitude toward the chosen option.

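### The mark for adequate knowledge, 8 of 15 correct/false items, lies at chance level, so the knowledge condition of the informed-choice rating separates knowledge from guessing poorly and dilutes the group difference

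*Protocol article*

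**What the plan says.** Under Attitude and knowledge, the protocol article tests knowledge with "a set of 15 items developed by experts in the field developed in a prior study". On the answer format it says: "For each item, the participant has to indicate whether a statement is correct or false". The items cover lifetime cancer risk and "benefits and harms about each preventive option, as well as lifestyle-related questions". A choice counts as informed when two conditions are met together: "adequate knowledge (at least eight correct knowledge items) about the option and a positive attitude toward the chosen option".

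The section describes no don't-know answer, no correction for guessing and no score per option, and it gives no reason for eight. Under Outcomes, knowledge and attitude are listed as secondary outcomes, and Table 1 schedules each at t0, t1 and t2. The informed-choice rating itself is defined only under Attitude and knowledge.

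**The concern.** With two answers per item, guessing gives a mean score of 7.5 out of 15, and eight is the first whole score above it. A mark at that point lets through many women who do not know the content, in both groups. A rule that passes uninformed women in both arms raises both rates and shrinks the difference between them.

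There is also a mismatch inside the rule. It asks for knowledge about the chosen option, but the count runs over a test that includes lifetime risk, the other options and lifestyle.

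At stake is the rating that puts the aim of informed decision-making into operation. The trial could report high informed-choice rates in both groups and a small difference even if coaching and the decision aid had clearly raised knowledge.

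**Working it through.** **Inputs from the protocol article.** 15 items; two answers per item, so a guess is right with probability 0.5; pass mark 8 (all from Attitude and knowledge). 199 women per group and 30% drop-out (Sample size), so 199 × 0.70 ≈ 139 per group. The document states no chance pass rate, so there is no figure of its own to reproduce.

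**1. Pure guessing.** X ~ Binomial(15, 0.5). The distribution is symmetric about 7.5, so P(X ≥ 8) = 0.500 exactly. For other marks:

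| Mark | P(pass by guessing) |
|---|---|
| ≥ 8 | 0.500 |
| ≥ 9 | 0.304 |
| ≥ 10 | 0.151 |
| ≥ 11 | 0.059 |
| ≥ 12 | 0.018 |

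**2. Partial knowledge.** A woman who knows k items and guesses the other 15 − k passes with probability P(Binomial(15 − k, 0.5) ≥ 8 − k):
- k = 0: 0.50
- k = 3: 0.81
- k = 5: 0.95
- k = 8: 1.00

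The pass rate rises with knowledge, but it is already high for women who know a third of the items or fewer.

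**3. Effect on the group difference (knowledge condition only).** Let p be the true share with adequate knowledge. Assume that all of these women pass and that the others guess. The observed share is p + (1 − p) × 0.5. The observed difference is then (p_IG − p_CG) × (1 − 0.5), which is half the true difference for any pair of shares. The shares below are assumptions; the document gives none. Power is two-sided at 0.05 with 139 per group.

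| True CG v IG | Seen at ≥ 8 | Power on true shares | Power on seen shares |
|---|---|---|---|
| 30% v 50% | 65% v 75% | 0.93 | 0.44 |
| 40% v 60% | 70% v 80% | 0.92 | 0.49 |
| 50% v 70% | 75% v 85% | 0.93 | 0.55 |

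**4. Which higher mark.** A higher mark also fails some women who do know the content. As a hard case, take 40% v 60% again, where knowledgeable women know 8 items and guess 7, and the others guess all 15.
- At ≥ 11, a knowledgeable woman needs 3 of 7 guesses: 0.773. Seen: 0.4 × 0.773 + 0.6 × 0.059 = 34.5% v 0.6 × 0.773 + 0.4 × 0.059 = 48.8%. Power 0.68.
- At ≥ 12, she needs 4 of 7: 0.500. Seen: 0.4 × 0.500 + 0.6 × 0.018 = 21.1% v 0.6 × 0.500 + 0.4 × 0.018 = 30.7%. Power 0.45.
- At ≥ 8, power is 0.49 as above.

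If knowledgeable women know 10 items, power is 0.86 at ≥ 11 and 0.77 at ≥ 12. If they know 12, it is 0.89 and 0.91. A mark of 11 improves on 8 in all three cases; a mark of 12 does not in the first.

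**5. Sensitivity to the answer format.** With a third answer and all three equally likely, P(Binomial(15, 1/3) ≥ 8) = 0.088.

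**The case against.** A reader might infer that the informed-choice rating cannot tell knowledge from chance at all. That goes too far. The pass rate climbs from 0.50 with nothing known to 1.00 with eight items known, so a real difference is weakened but not removed.

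Further points against the concern, and what stands of each:

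- **Pure guessing is a limiting case.** Every woman has at least one physician encounter on the prevention options, and some are already in the screening programme. This stands as a caution about the size. It does not rescue the mark, because women with a little knowledge pass even more often than guessers.
- **The attitude condition also has to be met.** So a guesser is rated informed at most half the time, and the shares and power above describe the knowledge condition alone. This stands.
- **Knowledge is also measured in its own right.** It is collected at three time points, and the Statistical methods section allows a comparison of scores without any mark. This stands and limits the damage, although the tests named there do not use the baseline score.
- **The questionnaire is not shown.** A don't-know box would lower the chance pass rate, to about 0.09 if three answers were equally likely. The article describes only correct or false, so 0.50 is the fair reading, but it is conditional on that.
- **A reader might also infer that a woman can be rated informed with every item on her chosen option wrong.** That needs at least eight items on other matters. The item split is not given, so only the weaker statement holds: she may be rated informed with little knowledge of that option.
- **A mark of 12 may look the natural remedy because few guessers reach it.** The calculation shows that it can lose as much power as the present mark if knowledgeable women know only about eight items.

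**Conclusion.** The concern holds in this form: the stated mark is the chance level for 15 two-way items, and following it as written misclassifies women in both groups. The pass probability of 0.50 for a guesser is exact, given a forced two-way answer. The halving of the difference on the knowledge condition is also exact if all women without adequate knowledge guess and all the others pass. The power figures depend on assumed shares and are illustrations only.

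Separately, the rule does not match its own wording, since knowledge about the option is judged by a count over the whole test.

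The weakness is confined to a rating built from secondary outcomes. Congruence on the Control Preferences Scale, the attitude condition and the continuous knowledge score are untouched. The mark should be changed, but the trial's main conclusion does not depend on it.

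**What to change.** Before any group comparison is seen:

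1. Raise the mark for adequate knowledge to at least 11 of 15 (guessing pass rate 5.9%).
2. Report the marks of at least 8 (50%) and at least 12 (1.8%) as sensitivity analyses.
3. Make the continuous knowledge score, adjusted for the t0 score that is already collected, the main knowledge analysis.
4. State whether knowledge is scored in total or per option, and bring the wording of the rule into line. State also whether the questionnaire offers a don't-know answer.

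This changes only the analysis definition; it needs no new data and no change in conduct. The cost is a lower reported share of informed choices, and some women with moderate knowledge will miss the higher mark, more so at 12 than at 11. For example, a woman who knows eight items and guesses the rest reaches 11 with probability 0.77 and 12 with probability 0.50.

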#### Stage of decision-making

To assess the stage of decision-making we used an adapted stage of decision-making (SDMS) [46]. The German Translation and adaption consists of one single item and four response options from “I haven’t begun to think about the choices” to “I have already made my choice” [47].

#### Anxiety and depression

Symptoms of anxiety and depression will be measured with the Hospital Anxiety and Depression Scale (HADS) [48, 49]. The HADS is a widely used instrument that comprises two scales, one of which assesses symptoms of anxiety, the other symptoms of depression. The 14 items are rated on a four-point Likert scale. The HADS shows good psychometric properties, with most studies reporting an internal consistency of Cronbachs alpha = 0.8 or higher.

